### Study Objectives

The primary objective is to evaluate the impact of 2 awareness-raising strategies against HPV by involving middle school students to increase vaccination uptake. Specifically, we aim to compare the proportion of students who initiated vaccination before and after the interventions. In addition, we will assess motivations and challenges encountered in both the serious game and ambassador classes, as well as overall student satisfaction and knowledge.

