**Methods:**

This protocol describes the design of a randomized, open-label, controlled trial aimed at evaluating the effectiveness of 2 awareness-raising interventions—peer learning and a card-based serious game—in improving HPV vaccination rates among middle school students in Réunion Island. The study will span an entire school year, beginning in August. Approximately 3600 students from 24 middle schools in Réunion Island will be included, with schools randomized into 3 groups of 8 each: (1) a control group receiving the existing national vaccination campaign initiated by the French public health institute; (2) ambassador classes, whose students will receive education about the HPV vaccine and later educate other students in the same school; and (3) serious game card group, where students can play and learn about HPV during a science class. The primary outcome will be the proportion of teenagers who initiate the vaccination process, compared across the 3 groups using appropriate statistical methods. Anonymized data will be collected at the end of the school year using social security records. Teenagers’ knowledge of HPV will be assessed both before and 3 months after each intervention, and satisfaction will also be evaluated after the intervention in each group.

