### Intervention

#### Control Group

The control group will consist of 8 randomly assigned middle schools. These schools will follow the existing vaccination campaign, without any modifications, as implemented by the French government. As vaccination campaigns are coordinated by the local Regional Health Agency, they are relatively uniform across all middle schools in Réunion, ensuring standardization and internal validity. Parents will receive information materials and consent forms through their children. Both parents are invited to sign the written consent form, which the child will then submit to the school counselor or school nurse. The counselor or nurse will forward the forms to the vaccination teams assigned to the area. This allows the vaccination teams, in coordination with the education staff, to schedule their visit to the school on a specific day and bring the appropriate number of vaccine doses corresponding to the consent forms received. Vaccination teams typically visit each school twice a year to administer 2 vaccine doses 6 months apart, usually in December (year Y) and June (year Y+1).

A preintervention questionnaire will be administered to assess students’ baseline knowledge about HPV (T0). The questionnaire will be standardized, anonymous, and identical for all participants. It will be available on tablets, computers, or on paper, depending on availability. A postintervention knowledge assessment will be conducted 3 months later (T1) using a questionnaire identical to the preintervention one, to evaluate changes in the rate of correct responses before and after the vaccination campaign.

The standardized knowledge questionnaire was developed by the research team and will assess students’ knowledge of HPV epidemiology, complications, and prevention (including vaccination; Multimedia Appendix 1). Each question requires a response of “yes,” “no,” or “I don’t know.” The questionnaire consists of 11 questions.

Vaccination status will be collected using the French social security system after anonymization of social security numbers (T3).

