### Measures

#### Primary Outcome: Evaluate New Tools to Improve Vaccination

The primary outcome of this study is the proportion of students in each group who initiate HPV vaccination by the end of the school year (at least one dose of the HPV vaccine).

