#### Secondary Outcomes

The secondary outcomes are as follows:

Evaluate the proportion of girls and boys in each group who initiate HPV vaccination by the end of the school year.Explore and assess the motivations and challenges perceived by students in the ambassador classes and by those participating in the serious games.Evaluate overall student satisfaction within each arm for descriptive purposes.Compare students’ knowledge before and after the intervention in each arm.

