### Data Collection, Management, and Monitoring

Pre- and postintervention knowledge questionnaires will be identical for all students (Multimedia Appendix 1). Satisfaction questionnaires will be tailored to the specific trial arm—ambassador class or serious game—to evaluate the unique aspects of each intervention (Multimedia Appendices 2 and 3). Data collection via questionnaires will be anonymized and conducted at the class level.

Vaccination status will be collected with the assistance of the French social security system, following anonymization of social security numbers.

All information required by the protocol must be recorded in the observation notebooks, and any missing data must be explained. Data should be collected as they are obtained and transcribed neatly and legibly. Data will be entered into an electronic observation notebook (electronic case report form) using Ennov Clinical software.

A clinical research associate appointed by the sponsor will regularly visit the investigator center—at study initiation, periodically during the research depending on the inclusion rate, and at study completion. During these visits, and in accordance with the risk-based monitoring plan (considering participants, logistics, impact, and resources), the following elements will be reviewed:

Nonopposition from participantsCompliance with the research protocol and defined proceduresQuality of data collected in the observation notebook, including accuracy, completeness, and consistency with source documents (eg, medical records, appointment books, original laboratory results)

A written monitoring report will be prepared for each visit.

An audit may be conducted at any time by individuals mandated by the sponsor and independent of the research team. Its purpose is to verify participant safety and rights, ensure compliance with applicable regulations, and assess the reliability of the data.

An inspection may also be ordered by a competent authority (eg, ANSM [Agence nationale de sécurité du médicament et des produits de santé] in France).

Both audits and inspections may be conducted at any stage of the research, from protocol development to publication of results and the handling of data generated during the study.

Investigators agree to comply with the sponsor’s requirements for audits and with the competent authority’s requirements for inspections.

Four follow-up visits will be scheduled (Textbox 2).

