We chose to use schools as units of randomization, rather than individual students.We will try to select schools that are geographically separate—ideally from different cities—to limit student interaction, although this remains subject to randomization.We will try to measure the extent of contamination at the end of the study by asking students whether they heard about HPV vaccination from students in other schools.Although blinding is not practically feasible for this study, students and teachers in control schools can be informed that they are part of a general public health campaign without knowing the specific educational strategies tested in other arms. We have planned an objective primary end point to compensate for this. Recovery of vaccination status will be carried out using the French social security system after anonymization of social security numbers.We plan continuous monitoring in the form of visits to establish quality controls throughout the study, including on-site visits and calls to school officials.We will use a mixed logistic model with random intercepts to assess the effect of the 2 interventions, compared with the control group, on the proportion of vaccinated individuals. This model will allow us to account for the cluster structure of the data. By including schools as random effects, we consider that each school may have a different baseline proportion of vaccinated individuals due to unmeasured factors. The interventions will be modeled as fixed effects. A mixed logistic model with a random intercept is an ideal approach for analyzing data in a cluster-randomized study (such as one involving schools) while accounting for contamination bias.

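### The primary aim is worded as a before/after comparison that contradicts the between-arm outcome and model, and the knowledge outcome names only within-arm change although controls take the same two tests

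*Protocol article*

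**What the plan says.** On vaccination, Study Objectives gives the specific primary aim as "we aim to compare the proportion of students who initiated vaccination before and after the interventions". The sentence names neither an arm nor a control. The Primary Outcome section defines "the proportion of students in each group who initiate HPV vaccination by the end of the school year". The abstract says this is "compared across the 3 groups using appropriate statistical methods". Study Limitations describes a mixed logistic model with a random intercept for school, used "to assess the effect of the 2 interventions, compared with the control group, on the proportion of vaccinated individuals". The Sample Size section assumes 30% in the control group and 45% in each intervention group by the end of the school year.

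On knowledge, the Secondary Outcomes list compares students' "knowledge before and after the intervention in each arm". The control arm completes the same T0 and T1 questionnaires, in its case "to evaluate changes in the rate of correct responses before and after the vaccination campaign". The Control Group section adds: "The questionnaire will be standardized, anonymous, and identical for all participants". Data Collection, Management, and Monitoring says: "Data collection via questionnaires will be anonymized and conducted at the class level". No code linking a student's two questionnaires is described.

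**The concern.** An objective, its outcome and its analysis should describe one comparison. Here the objective describes another. A reader of Study Objectives would expect a change over time, while a reader of the outcome and model would expect a difference between randomized groups. If the trial is reported against its stated aim, it will either present an analysis it has no data for or appear to have changed its question.

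For knowledge the wording matters more, because it is the only comparison the article gives for that outcome. A rise from T0 to T1 in an intervention arm does not show that the intervention worked, since some rise is plausible in control as well. The randomized control data that would separate the two will exist, but the outcome as written does not use them.

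**Working it through.** **1. The primary contrast, place by place.**

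| Place | Comparison stated |
|---|---|
| Study Objectives | before against after; no arm named |
| Abstract, Methods | across the three groups |
| Sample Size | 30% control against 45% intervention, end of year |
| Primary Outcome | proportion in each group, end of year |
| Study Limitations | each intervention against control, school as random intercept |

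Four places agree and one differs. The planned effect is 45 − 30 = 15 percentage points, a difference between arms at one time point.

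**2. Whether a before/after contrast could be formed.** It would be P(after) − P(before).

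- P(after) comes from the social security system at T3, around July (Figure 1 legend, Settings, and each of the three arm descriptions).
- P(before) is not scheduled anywhere. T0 is a knowledge questionnaire only.
- The follow-up visits textbox describes the T3 data as initiation during the school year. If only those initiations count, P(before) is zero by definition and the contrast reduces to the T3 proportion.

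**3. What within-arm knowledge change contains.** T0 is taken just before the programme, which runs between September and December. T1 follows about 3 months after it ends, so roughly December to March. The first vaccination campaign is usually in December. Write the average T0-to-T1 change as

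- intervention arm: I + C + T + R
- control arm: C + T + R

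where I is the intervention, C the campaign, T the passage of time and R the effect of repeating the same 11 questions. Within-arm change estimates the whole sum. The difference between arms estimates I, provided the control questionnaires are given over a comparable interval. The Control Group section describes the campaign as fairly uniform across schools, which supports treating C as common to the arms. No knowledge scores for this setting are given, so the terms cannot be sized.

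**4. How much student-level linkage matters for the between-arm contrast.** The article gives an intracluster correlation (ICC) of 0.1 for vaccination and 190 students per college. It gives none for knowledge, so the ICC here is an assumption. With total variance set to 1, the variance of a school mean is ICC + (1 − ICC)/190, and the student-level share is [(1 − ICC)/190] divided by that sum.

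- ICC 0.10: 0.90/190 = 0.0047; 0.0047/0.1047 = 4.5%
- ICC 0.05: 0.95/190 = 0.0050; 0.0050/0.0550 = 9.1%
- ICC 0.02: 0.98/190 = 0.0052; 0.0052/0.0252 = 20.5%

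At the protocol's ICC nearly all the uncertainty lies between schools, which a class or school mean T0 score can address without linking individuals.

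**The case against.** The strongest reply is that Study Objectives contains a drafting slip and nothing depends on it. The outcome, sample size, abstract and model all compare arms, and every arm is exposed to the same national campaign. That stands, and it limits the primary part of this point to a mismatch in wording.

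On knowledge, the reply is that this is a secondary outcome, that Statistical Analysis applies intention-to-treat by randomized group to comparative analyses of the end points, and that model detail belongs in an analysis plan not shown here. Leaving the model to that plan is fair. But the article does state a comparison for knowledge, and the one it states is within arm.

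Three stronger readings are tempting and are not supported.

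- A reader might infer that the primary result would credit the campaign and the time trend to the interventions. It would not, because the model is against a concurrent randomized control.
- A reader might take 30 − 21.5 = 8.5 points as the rise expected without intervention. The 21.5% is for 12-year-olds at the end of 2023, whereas the trial is expected to start in August 2026. No baseline for the trial cohort is given, and Expected Outcomes anticipates stable or only slightly higher coverage within a year.
- A reader might conclude that anonymity forces T0 and T1 to be treated as independent samples. Class-level collection still allows pairing by class or school. A linking code is not described, but it is not ruled out either.

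**Conclusion.** The point holds in two limited parts.

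First, the specific primary aim contradicts the outcome, sample size and model, and no baseline vaccination data are scheduled to support it. The consequence is an unclear objective, with no numerical bias in the planned 15-point between-arm comparison.

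Second, the knowledge outcome is fixed as within-arm change, which cannot be attributed to the intervention, even though control data from the same questionnaire will be available. How far the change would mislead is unknown. The conclusion needs only that the campaign, time or retesting could move scores in control, and the article itself plans to measure change in that arm.

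The first part rests on the text alone. The second assumes that no between-arm knowledge comparison is specified in a document not shown. Both are worth correcting before the study starts.

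**What to change.** 1. **Study Objectives.** Restate the specific aim as comparing the proportion of students who initiate vaccination by the end of the school year between each intervention arm and the control arm.
2. **Secondary Outcomes.** Restate the knowledge item as a comparison of T1 knowledge between each intervention arm and control, adjusted for T0, with school as a random effect. Keep within-arm change as descriptive.
3. **T0 adjustment.** With questionnaires as now described, adjust for the class or school mean T0 score.
4. **Optional.** Put a non-identifying student code on both questionnaires to allow individual adjustment.

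Items 1 to 3 cost only wording, and no extra data are needed. Item 4 means declaring pseudonymous rather than anonymous questionnaire data in the data protection file. That is a small cost while the approval is still in progress, but the code cannot be added once the questionnaires have been collected.

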### Settings

This study is scheduled to start in August-September (the beginning of the school year) and is expected to last approximately 1 school year, concluding in July (Figure 1). The research team will perform randomization to allocate 8 colleges per arm.

**Figure 1 figure1:**
[figure not shown]
Participants timeline 
T0 : pre-intervention questionnaire
T1 : post intervention questionnaire at 3 months
T2 : only for ambassador classes : information by ambassador classes to their peers in 7th grade class
T3 : collection of vaccination status.

In August, at the beginning of the new academic school year, parental consent will be collected.

In September, children will be enrolled after confirming that their parents do not object to participation.

Vaccination campaigns typically occur in December and June, with the first dose usually given in December and the second dose in June, although vaccination can also be initiated with the first dose in June, all scheduled before school holidays.

Between September and December, the following events will occur:

In the ambassador group, a facilitator, after receiving prior training, will introduce HPV to students in the ambassador classes using a standardized slideshow identical across all classes. These students will then be responsible for conveying this information to other seventh-grade classes in their school. They will have the autonomy to choose the format for delivering the information to their peers (eg, games, presentations, films, posters, slideshows, comics).In the serious game group, 1 facilitator will explain the functioning and rules of the game to volunteer science teachers. The game is designed so that teachers can work independently with the students. Teachers may choose when to conduct the serious game during school classes before the vaccination campaigns.

At the end of the school year, around July, vaccination status will be collected using the French social security system, following anonymization of social security numbers.

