## Introduction

Human papillomavirus (HPV) is a widespread sexually transmitted infection that affects more than 1 in 5 people globally [1]. It is estimated that about 80% of men and women will be exposed to HPV at some point in their lives. With a global prevalence of 31% in men and 32.1% in women [2,3], HPV represents a major public health concern due to its established role in the development of multiple cancers [4], most notably cervical cancer, which remains the fourth most frequent cancer in women worldwide. The World Health Organization reported 660,000 new cervical cancer cases and 350,000 related deaths in 2022. In France, HPV is responsible for over 6400 cancers annually, including cervical, vulvar, vaginal, penile, anal, and oropharyngeal cancers. On Réunion Island, cervical cancer is the third most common cancer in women.

Prevention of cervical cancer is mainly based on screening with Papanicolaou (Pap) smear tests and HPV vaccination. Despite the proven safety and effectiveness of HPV vaccines in reducing the incidence of precancerous lesions and genital warts [5-7], vaccination coverage in France remains insufficient. As of 2023, only 45% of girls and 16% of boys aged 16 were vaccinated [8]. In Réunion Island, coverage is even lower: in 2022, only 12.7% of adolescents under 16 had received at least one dose of the HPV vaccine. Following the national vaccination campaign launched in 2023, only 6.8% of seventh-grade students were vaccinated at school in Réunion. Taking into account children vaccinated outside school by their general practitioner, the rate modestly increased to 27% for girls and 16% for boys. Nevertheless, these figures remain far from the thresholds needed to achieve herd immunity and effective cancer prevention [9].

The low uptake in Réunion Island may be attributed to a lack of information, fear of adverse events, and limited engagement from both health care professionals and families [10,11]. In countries such as Australia, Belgium, Portugal, and the United Kingdom, school-based HPV vaccination programs have achieved coverage rates exceeding 80% [12]. These programs reduce access barriers, promote equity, and provide opportunities for engaging educational interventions.

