Follow-up visits.1. Visit 1 (T0)This visit will take place during school hours, just before the start of the awareness program (arms 2 and 3).Students will complete a questionnaire assessing their knowledge of human papillomavirus (HPV).The estimated completion time is a maximum of 10 minutes.2. Visit 2 (T1)This visit will take place during school hours, approximately 3 months after the end of the awareness program.Students will complete the same questionnaire to assess their postintervention knowledge.The estimated completion time is a maximum of 10 minutes.3. Visit 3 (T2)This visit will take place only in the middle schools assigned to the “ambassador classes” arm to assess the satisfaction of students receiving the intervention from their trained peers.A member of the research team will be present during the ambassador class intervention to ensure that essential information is accurately conveyed.The estimated completion time is a maximum of 10 minutes.4. Visit 4 (T3)At the end of the study, qualitative interviews will be conducted to explore the motivations and challenges experienced by teachers, parents, and students participating in the study.Each participant will receive information about the study and will provide consent for audio-recording of their interview.The interviews will then be transcribed anonymously using qualitative data analysis software.5. End of research visitThe end-of-research visit marks the final data collection, which may include qualitative interviews or vaccination data.This visit will also be used to collect information on HPV vaccination initiation during the school year (at least one dose counts) for each student, with assistance from the Social Security system via anonymized social security numbers.Within 1 year of the end of the research or its early termination, a final report will be prepared and signed by both the sponsor and the investigator.This report will be submitted to the competent authority.Additionally, the sponsor will provide the Committee for the Protection of Persons with a summary of the final report within 1 year of the study’s conclusion.

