## Results

### Preliminary Findings

A first draft of the serious game was created with funding obtained in March 2024 (Innovation Prize of University Hospitals).

As of May 2025, it was tested in 1 middle school in Réunion Island across all seventh grades, with the approval of the school director and teachers, before the vaccination campaign. The game is intended to be used by teachers alone, without the help of a game animator, to enhance reproducibility.

Children were engaged by the game, and their intention to vaccinate was higher than in other schools. Among the 189 students in seventh grade at that school, vaccination teams had initially received consent for 10 students to be vaccinated. After the intervention/serious game, more students submitted signed consents, and a total of 25 (13.2%) students were vaccinated. In other schools in Réunion during that campaign, vaccination coverage did not exceed 7% (986/14,500, 6.8%).

Although the serious game has been developed, some minor changes need to be considered following this first experience with children. Once finalized, production of several copies will be launched. As registrations are in progress, the study is expected to start during the academic year in August 2026.

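### The primary endpoint is read around July from social security records alone, and the protocol does not establish that doses given at school, especially in June, will be in that file by then

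*Protocol article*

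**What the plan says.** **Endpoint.** Measures (Primary Outcome) sets it, by arm, as the share of students observed to "initiate HPV vaccination by the end of the school year (at least one dose of the HPV vaccine").

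**Source and date.** Settings states: "vaccination status will be collected using the French social security system, following anonymization of social security numbers", with collection in about July. Data Collection, Management, and Monitoring repeats the source: "Vaccination status will be collected with the assistance of the French social security system, following anonymization of social security numbers". Textbox 2 says the information is gathered "for each student, with assistance from the Social Security system via anonymized social security numbers". The Abstract, the descriptions of all three arms and Study Limitations also name social security and nothing else. Study Limitations relies on this objective endpoint to offset the lack of blinding.

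**How school doses are given.** Under Control Group, families return signed forms to the school. The forms go to the vaccination teams, who visit and "bring the appropriate number of vaccine doses corresponding to the consent forms received". Settings places the campaigns typically in December and June. The first dose is usually in December, but a first dose in June is allowed. Teachers run the card game before the campaigns.

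**Two channels in the protocol's own figures.** The Introduction gives 6.8% of seventh-grade students vaccinated at school, then continues: "Taking into account children vaccinated outside school by their general practitioner, the rate modestly increased to 27% for girls and 16% for boys".

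**Pilot.** Preliminary Findings starts from consents for 10 of 189 students. After the game, "more students submitted signed consents, and a total of 25 (13.2%) students were vaccinated". The comparison figure for other schools in that campaign is 986/14,500 (6.8%).

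**The concern.** The protocol fixes both the source and the date of its primary endpoint. It does not say whether a dose given by a school team reaches the social security file as a record for that child, or with what delay. The team brings these doses to the school, so they take a different route from a dose given by a general practitioner. A first dose in June may be only weeks old when status is collected around July, and it counts towards the endpoint.

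This bears on the treatment effect as well as on the level of coverage. If an intervention adds doses partly through the school campaign, the doses it adds are partly the ones at risk of not being seen. Using the same file in every arm does not prevent this. Under-recording of one channel removes more doses from the arm with more doses in that channel, which biases the comparison towards no effect. An objective endpoint guards against biased assessment, but it does not guarantee complete capture. Doses that were never collected cannot be recovered at the analysis stage.

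**Working it through.** **Inputs from the protocol.** Control 30% and intervention 45% (Sample Size); 6.8% vaccinated at school, and 27% of girls and 16% of boys when doses outside school are added (Introduction); 25/189 and 986/14,500 (Preliminary Findings); 8 colleges per arm, 190 students per college, ICC 0.1, two-sided 5% (Sample Size, Statistical Analysis).

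**The protocol's own figures reproduce.** 25/189 = 13.2%. 986/14,500 = 6.8%. The planned gain is 45 − 30 = 15 points.

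**Assumed quantities (not in the protocol).**
- g: share of the gain that comes through school doses.
- v: share of school doses visible in the file when it is read, taken as equal in all arms.
- b: percentage points of school doses that would occur in both arms anyway.

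**Formula.**
- Observed control = 30 − b(1 − v)
- Observed intervention = 45 − (b + 15g)(1 − v)
- Observed gain = 15 − 15g(1 − v) = 15 × (1 − g(1 − v))

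The common part b cancels. What is lost is the part of the gain made through school.

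**Observed gain in points.**

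| | v = 1 | v = 0.5 | v = 0 |
|---|---|---|---|
| g = 0 | 15 | 15 | 15 |
| g = 0.5 | 15 | 11.25 | 7.5 |
| g = 1 | 15 | 7.5 | 0 |

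**Only June first doses lost.** Let j be the share of school doses that are June first doses not yet recorded, so v = 1 − j. With g = 1, the observed gain is 15 × (1 − j): 13.5 points at j = 0.10, 11.25 at j = 0.25 and 7.5 at j = 0.50. With g = 0.5 it is 15 × (1 − 0.5j): 14.25 points at j = 0.10 and 11.25 at j = 0.50.

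**What this does to power (illustration).** Take b = 6.8 and g = 1. At v = 0.5 the observed rates are 30 − 3.4 = 26.6% and 45 − 10.9 = 34.1%. With 8 colleges of 190 and ICC 0.1, the effective size is 8 × 190/19.9 = 76.4 per arm. Power is about 48% at v = 1 and 17% at v = 0.5. At an assumed ICC of 0.02 it is about 98% and 54%. That the full-capture figure at ICC 0.1 is below the stated 90% is a separate matter and plays no part here.

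**The case against.** The strongest reply is that the protocol nowhere says school doses are missing or late in the social security file. Whether they are is a fact about a national system that these documents do not describe. The article is also a condensed account, and its wording in two places (with the assistance of the system) does not exclude a further source or a later extraction. This stands to the extent that the point is an unaddressed risk and not a demonstrated error. It does not dispose of the point. The article goes beyond silence: it fixes one source and one time, repeats the source throughout, and rests its defence of the open-label design on it.

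Four stronger readings are tempting, and the documents do not support them.

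- *The gain will come mainly through school, so the trial would read as null.* In the Introduction, school doses are 6.8% against a simple mean of (27 + 16)/2 = 21.5% overall. That is 6.8/21.5 = 32%, so about two-thirds of coverage lies outside school. The pilot reports only the teams' consents and doses and says nothing about general practitioner doses, so it cannot tell us g.
- *An effective arm could look harmful.* This would need children to move from general practitioner to school vaccination, which nothing in the documents suggests.
- *Textbox 2 makes vaccination data optional.* One sentence says the final visit may include them, but the next commits to collecting vaccination initiation for each student.
- *The teams belong to the Regional Health Agency.* Control Group says only that the Agency coordinates the campaigns.

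The timing risk should not be overstated either. First doses are usually given in December, about seven months before July, so June first doses are the exception.

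**Conclusion.** The point holds as a conditional one. The protocol reads its primary endpoint from a single named source around July and does not establish that this source holds school-team doses per child, or holds June doses by then. If capture is incomplete, the effect is attenuated. The planned 15 points becomes 11.25 with g = v = 0.5, and 7.5 with g = 1 and v = 0.5. If only June first doses are lost, they make up 10% to 50% of school doses, and the whole gain runs through school, it becomes 13.5 to 7.5 points. All of these rest on assumed values of g, v and j, and on equal capture across arms. Attenuation is the realistic risk. A null result needs both extremes together, with all of the gain through school and no school dose visible. If the sponsor can document complete and timely capture, the concern is settled. The change is worth making before the start because matching on identifiers cannot be arranged once they have been anonymized.

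**What to change.** 1. Define initiation as a first dose dated up to the last day of the school year. Keep that cut-off for dose dates, but extract the data some months later so that June doses have time to be recorded.
2. Before the trial, confirm that school-team doses appear per child in the social security file, and with what delay, and state this in the protocol. The pilot school's 25 doses could serve as a test if identifiers and permission can be obtained; the article reports only counts.
3. If capture cannot be shown, count a dose found in either the social security file or the school teams' administration records. Match these records before anonymization and in the same way in all three arms.

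**Cost.** Results come some months later. Step 3 adds a data-sharing step to the data-protection application, which Ethics Approval says is still in progress, and the sponsor must first check that the teams keep per-child records. No extra participants or school visits are needed.
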